#### Analysis of behavioural outcomes

2.13.2

Group effects on oral health behaviour between the conditions will be assessed by predicting six and twelve-month follow-up scores from group membership. To minimise the probability of Type 1 error, multivariate analyses will be used. Subsequent univariate analyses will identify specific variables affected by group. Planned comparisons will test the hypotheses that; TL leads to greater positive oral health behaviour change than V, and QLF leads to greater positive behavioural change than V. Separate analyses will examine changes from baseline to 6 months and from baseline to 12 months.

Moderation analyses involve the modelling of two-way interaction effects from the product of the predictor and moderator variables and testing the hypothesis that the interaction term uniquely predicts behavioural change controlling main effects terms [47]. Regression analyses will be used to test this hypothesis. Demographic, dental health and dental visiting variables will be tested as potential moderators.

Mediation analyses assess the extent to which intermediate variables (mediators) explain variance shared between predictor and outcome variables. Again, this analysis will be performed only where between group differences in behavioural change have been identified. Our mediation analysis strategy is based on recommendations by Zhao et al., [48] who specify pre-conditions that the predictor (group membership) be linked to the mediator (EPPM variables), and that the mediator be linked to the criterion (behavioural change) controlling the predictor. When these are established, path analysis can be used to estimate the mediation effect. To statistically test mediation, we will use a bootstrapping method [49]. All potential mediators will be assessed in the same analysis, reducing the likelihood of Type 2 error that would be associated with testing mediators separately.

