#### Secondary outcomes

2.8.2

*Patient-Clinician communication measured immediately after the intervention*•Communication Assessment Tool (CAT) [30] 15 item stem from *1*=*very poor to 5*=*excellent*

*Self-reported behaviour change between baseline and 6 months post-intervention; and between baseline and 12-months post-intervention*•Oral hygieneoTooth-brushing frequency *‘How often do you brush your teeth nowadays?’ (1* = >*2x/day, 2*=*Twice a day, 3*=*Once a day, 4* = <*once a day, 5*=*Never)* [31]oDuration of tooth-brushing *‘How long do you clean your teeth for nowadays? (1*=>*3 min, 2* = *3 min, 3* = *2 min, 4* = *1 min, 5* = < *1 min)* [32]oFrequency of interdental cleaning *‘How often do you do interdental cleaning?* e.g. *with floss, interdental brushes, tooth sticks etc.?’ 1*= > *once a day, 2*=*At least twice a week, 3*=*Weekly, 4*=*Monthly, 5*=*Never* [32]•Use of FluorideoFluoride toothpaste (prescribed)oFluoride mouth-rinse•Dietary sugaroFrequency eating/drinking 6 items *‘How often, on average do you eat or drink these things?’ 1*=*More than once a day to 7*=*Never* [33]oFrequency sugar in tea and coffee *‘Do you usually have sugar (not artificial sweetener) in hot drinks like tea and coffee?’* [32]•Smoking [34].oCurrent smoker excluding e cigarettesoAverage number of tobacco items smoked

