**Assessments – self report**					
Patient demographics	x				
REALM-R	x				
WTP	x				
Dental visiting history/experience	x				
Dental anxiety (MDAS)	x				
Self-assessed oral health	x	x	x	x	x
Oral health behaviours: toothbrushing, diet, fluoride and smoking	x	x	x	x	x
EPPM and behaviour change predictors	x	x		x	x
Patient/clinician communication (CAT)	x				

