#### Analysis of clinical outcomes

2.13.3

Clinical outcomes will be analysed at the first short term follow-up visit, no more than three months post-randomisation. All QLF images will be rated as good/poor quality by the assessor (blinded to group allocation). Those not judged to be of sufficient quality to accurately generate the outcome variables will be excluded from the analysis. Analysis of the three QLF generated variables will use general linear models, with value of the variable of interest at the first short-term follow-up appointment as the outcome variable, and intervention group allocation as a fixed factor. Baseline value of the variable of interest will be included as a covariate. All analyses will follow the intention to treat principle as far as is practically possible.

Basic Periodontal examination (BPE) scores will be analysed by categorising each patient into one of four outcome categories. 1 – stable healthy (code 0 at baseline and follow-up), 2- stable bleeding (code 1 or greater at baseline and follow-up), 3 – change to bleeding (code 0 at baseline, code 1 or greater at follow-up), and 4 – change to healthy (code 1 or greater at baseline, code 0 at follow-up). The analysis will use multinomial logistic regression to test the effect of intervention group on outcome, with the primary hypothesis of interest between groups 2 and 4.

Multiple imputation analyses will be carried out to investigate the robustness of the results to missing data. Using all the data which is available, including baseline variables, five complete case data sets will be imputed, and each analysed in the same way. The results can then be combined, and compared with the analysis excluding missing data, to assess whether this would be likely to change the overall conclusions.

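### The behavioural analysis alternates between follow-up score and change from baseline, never states the baseline-adjusted model used for the QLF outcomes, and makes a Type 1 error statement that holds only for the global test

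*Protocol article*

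**What the plan says.** Protocol article, section 2.13.2, opens by stating that group effects on oral health behaviour "will be assessed by predicting six and twelve-month follow-up scores from group membership". No covariate is named. The paragraph closes differently: "Separate analyses will examine changes from baseline to 6 months and from baseline to 12 months". Its hypotheses are also worded as change: "TL leads to greater positive oral health behaviour change than V, and QLF leads to greater positive behavioural change than V". Section 2.8.2 heads these outcomes "Self-reported behaviour change between baseline and 6 months post-intervention; and between baseline and 12-months post-intervention".

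Baseline values exist. In Table 1 the row "Oral health behaviours: toothbrushing, diet, fluoride and smoking" is marked at baseline, visits 2 and 3, 6 months and 12 months. For the three QLF variables, section 2.13.3 takes the follow-up value as the outcome with group as a fixed factor, and adds: "Baseline value of the variable of interest will be included as a covariate".

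On multiplicity, section 2.13.2 says: "To minimise the probability of Type 1 error, multivariate analyses will be used. Subsequent univariate analyses will identify specific variables affected by group". No adjustment is stated for the univariate step, for the two planned comparisons (TL v V and QLF v V) or for the two time points. Section 2.13 promises a detailed statistical analysis plan before data analysis; it is not shown.

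**The concern.** Two different outcome definitions stand in one paragraph with no order between them. They can disagree, because they treat a chance difference between arms at baseline in opposite ways. The follow-up-only analysis carries part of it into the result, and the change score over-corrects for it. Baseline adjustment does neither and is at least as precise as both. The protocol already uses it for the QLF outcomes. Precision matters here because section 3 itself warns that long-term follow-up may be difficult.

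Change scores also suit several items in section 2.8.2 poorly. Current smoking is yes/no. The interdental cleaning codes run from more than once a day through weekly and monthly to never, so one-point steps are not equal amounts of change.

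On Type 1 error, the univariate step exists to say which behaviours changed. That is where an omnibus test stops protecting. Section 2.13.2 also makes mediation analysis conditional on a between-group difference in behaviour change, so a false single-behaviour result could set off an analysis of the EPPM variables.

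**Working it through.** **Inputs from the documents.** 133 per arm, 80% power and α = 0.05 (section 2.10; sidedness not stated, two-sided assumed); 53% attending both baseline and follow-up in a comparable non-randomised study (section 3), so 133 × 0.53 ≈ 70 per arm as a scenario; two planned comparisons and two time points (section 2.13.2).

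**Assumptions.** Baseline/follow-up correlation r of 0.3 to 0.7 with equal variances; 5 or 9 behavioural outcomes; between-outcome correlation of 0 or 0.3; normal scores. Nine is the count in section 2.8.2 with the six sugar items taken as one score: three oral hygiene, two fluoride, two sugar and two smoking outcomes. With the six items separate it is 14.

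**The plan's own figures.** The two-sample normal formula returns 63 per arm for 0.5 SD and 145 for 0.33 SD, as stated. For plaque, 133 per group gives 81.4% power for 3.5 with SD 10. These are not in dispute. The article states no power or familywise error for the behavioural outcomes.

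**Step 1: precision.** Relative to the follow-up-only variance, change has 2(1 − r) and the adjusted analysis has 1 − r² = (1 − r)(1 + r). Since 1 + r ≤ 2 and r² ≥ 0, the adjusted variance never exceeds either alternative.

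| r | follow-up only | change | adjusted |
|---|---|---|---|
| 0.3 | 1.00 | 1.40 | 0.91 |
| 0.5 | 1.00 | 1.00 | 0.75 |
| 0.7 | 1.00 | 0.60 | 0.51 |

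Below r = 0.5, change is less precise than leaving baseline out.

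Power for an illustrative 0.35 SD difference (r = 0.3/0.5/0.7):

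| per arm | follow-up only | change | adjusted |
|---|---|---|---|
| 133 | 81.4% | 67.4/81.4/95.8% | 84.9/90.9/97.9% |
| 70 | 54.4% | 41.7/54.4/76.2% | 58.3/66.7/82.6% |

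**Step 2: chance imbalance.** If the arms differ by d at baseline, the follow-up-only estimate is shifted by r·d and the change estimate by −(1 − r)·d. The adjusted estimate is not shifted. Averaged over randomisations, all three are unbiased.

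**Step 3: Type 1 error.** Three arms were simulated with a Wilks omnibus test at 0.05 and, if it was significant, each behaviour tested at 0.05 without adjustment (2,500 runs per scenario).

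- No behaviour affected: at least one false claim in about 4-6% of runs per time point. Over two time points, if independent, 1 − 0.95² = 9.75% at a nominal 5% each.
- One behaviour truly different (0.5 or 0.8 SD in both intervention arms), 133 per arm: chance of at least one false claim among the others:

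| outcomes | univariate F tests | two planned comparisons |
|---|---|---|
| 5 | 16-18% | 29-32% |
| 9 | 29-34% | 45-52% |

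Hand check with the gate fully open: 8 unaffected behaviours at 0.05 give 1 − 0.95⁸ = 33.7%, close to the top F-test figure. For the planned comparisons, 16 independent tests would give 1 − 0.95¹⁶ = 56%. The simulated figure is lower because the two contrasts share the V arm.

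**Step 4: cost of strict adjustment.** Holm over 9 × 2 = 18 tests starts at 0.05/18 = 0.0028, z ≈ 2.99. At 70 per arm and r = 0.6, with adjusted SD factor √(1 − 0.36) = 0.8, the detectable difference at that first step is (2.99 + 0.84) × √(2/70) × 0.8 ≈ 0.52 SD. Without multiplicity adjustment it is 2.802 × √(2/70) = 0.47 SD (follow-up only), × √0.8 = 0.42 (change) and × 0.8 = 0.38 (baseline-adjusted).

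**The case against.** The strongest case against has four parts.

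**Baseline is used.** A reader might infer from the opening sentence of section 2.13.2 that the trial discards its baseline scores. The documents do not support that: the same paragraph analyses change, its hypotheses are about change, and section 2.8.2 defines the outcomes as change. What stands is that two forms alternate and neither is the adjusted model.

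**Covariates and link functions belong in the statistical analysis plan.** An article may leave them there, and silence alone would be no finding. But section 2.13.2 is not silent: it names two specific analyses, and a later plan that follows it would inherit both. The later plan may also settle the matter.

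**The gain is modest and nothing is biased.** This is correct. A reader might infer systematic bias; randomisation rules that out for both stated forms. Against change scores the gain shrinks as r rises. The 53% retention comes from appointment attendance in a different study, whereas this trial's 6- and 12-month data are collected by telephone, email or post. The 70-per-arm figures are therefore a scenario and not a forecast.

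**The Type 1 criticism assumes a procedure.** The article does not say MANOVA, says minimise rather than control at 5%, and is only silent about adjustment. A reader might also take the upper figure of about one in two as a property of the plan. It needs nine outcomes, a true effect and both contrasts tested on every behaviour; with five outcomes and F tests it is 16-18%. Under the global null the assumed procedure behaves as intended. These are secondary outcomes, the primary being WTP, so strict familywise control is a choice and not a requirement.

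**Conclusion.** The point holds in a limited form. Section 2.13.2 does not settle whether the behavioural outcome is the follow-up score or the change, and neither version is the baseline-adjusted model that section 2.13.3 uses. The loss is one of precision and of exposure to chance imbalance. Compared with adjustment at r = 0.3/0.5/0.7, follow-up only has 1.10/1.33/1.96 times the variance (1/0.91, 1/0.75, 1/0.51), and change has 1.54/1.33/1.18 times (1.40/0.91, 1.00/0.75, 0.60/0.51). The correlations are assumed. The formulas apply to outcomes treated as scores and are only a guide for ordinal and yes/no items.

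The Type 1 point is secondary and conditional. If the multivariate step is an omnibus gate followed by unadjusted tests, the stated protection covers the global null only. With one real effect, the chance of a false single-behaviour claim is about 16-34% or 29-52%, depending on the test used, for 5 to 9 assumed outcomes at 133 per arm. Neither point touches the primary WTP analysis.

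**What to change.** In the statistical analysis plan, replace the follow-up-only and change-score versions with one main analysis per behaviour and time point. Model the 6- or 12-month value on arm, the same behaviour at baseline, and practice (the stratification factor in section 2.7). Use a linear model for scores and an ordinal or logistic model for ordinal or yes/no items. Present TL v V and QLF v V from that model. This needs no new data or patients, only wording.

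For multiplicity, choose one of two courses and say so:

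- Keep the multivariate test, state that its Type 1 protection applies to the global hypothesis only, and label single-behaviour results, and any mediation analysis that they trigger, as exploratory. This costs no power but limits what can be claimed.
- Apply an adjustment such as Holm across behaviours and the two contrasts, stating whether 6 and 12 months form one family or two. This supports claims about named behaviours, but at the first step it costs more than baseline adjustment gains (the 0.52 SD in the working, against 0.42 to 0.47 SD for the stated forms without multiplicity adjustment).

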### Predictor and moderator variables

2.9

*Patient socio-demographic characteristics*•Area level deprivation based on home postcode (IMD) [36].•Employment status [36] response from *1*=*employed/self-employed full-time, 2*=*employed or self-employed part-time, 3*=*unemployed at the moment, 4* = *full-time education*•Household income (before deductions e.g. income tax) [37] *according to 9 categories given as weekly or yearly amounts, ranging from 1* = *£0 to 9* = *over £52,000* per *year*•Highest level of education response from *1* = *GCSE/NVQ level 1 or similar, to 5* = *postgraduate degree* [37].•Literacy using the Rapid Estimate of Adult Literacy in Medicine (REALM) [38]. The 8 medical test words, as well as the 3 practice words will be printed and shown to participants on an A4 laminated sheet, but with the American spelling of anemia changed to the English version (anaemia).*Patient dental visiting behaviour, dental anxiety and previous dental experiences*•Dental visiting: *‘In general, do you go to the dentist for: 1*=*a regular check-up, 2*=*an occasional check-up, 3*=*/only when having trouble with my teeth/dentures?’* [31]. *‘How many times have you been to the dentist in the last five years purely for a check-up?’* [31]•Previous pain experience: *‘Have you ever experienced dental pain bad enough to make you go to the dentist (tick all that apply): 1*=*currently in pain, 2*=*In the last 6 months, 3*=*6 months to 2 years ago, 4*=*more than 2 years ago, 5*=*never)’* [31].•Previous experience of dental treatment: *‘Have you ever had fillings/teeth extracted (taken out)/a dental bridge or a tooth crowned/a root canal treatment/a scale and polish?’* [31]•Dental anxiety: The Modified Dental Anxiety Scale (MDAS) [39].*Dental provider characteristics*•Dental practice•Clinician ID delivering information*Oral health*•Number of natural teeth as recorded by the dentist at the check-up*Risk perception and behaviour change predictors/moderators (based on the EPPM model)* [20]•Perceived threat (severity) *‘How serious would it be to you if* [negative outcome] *were to occur,* response from *1*=*not at all serious to 5*=*absolutely serious* Five possible negative outcomes of poor oral health were identified in earlier qualitative work: *‘your teeth were to make you feel uncomfortable when smiling, talking and laughing in front of people; people thought you had failed to look after your own teeth; your teeth were to become more painful and sensitive; you were to need treatment which meant spending more time at the dentist; you were to need treatment which you could not afford’*•Perceived threat (susceptibility) ‘*If you do not follow the dentist's advice, how likely is it that* [same 5 negative outcomes] *will occur*’ response from *1*=*absolutely unlikely to 5 absolutely likely*•Self-efficacy ‘*Please consider how confident you are that you can perform the behaviour properly, regularly and on a long-term basis for* [target behaviour]’ *response* from *1*=*not at all confident to 5*=*absolutely confident*.•Response efficacy ‘[target behaviour] *means I am less likely to have dental problems*’ responses from *1*=*Absolutely disagree to 5*=*Absolutely agree*•Message Fear ‘*How much did the advice you received make you feel … frightened/tense/nervous/anxious/uncomfortable*’ response from *1*=*not at all to 5*=*very much*•Affect regarding threat ‘*How would you feel how if you experienced* [negative outcome] [40]; *and* ‘*How vulnerable would you feel if you experienced* [negative outcome] [41] responses from *1*=*not bad to 5*=*absolutely bad*•Danger control response measured using 3 items: ‘*How likely it will be before your next appointment that you will. 1) follow the advice given by the dentist completely; 2) follow some of the advice given by the dentist 3) talk to someone about the advice the dentist gave you*’ response from *1*=*absolutely unlikely to 5*=*absolutely likely*•Fear control response measured using 4 items with stems: 1) Defensive Avoidance: ‘*I prefer not to think about the advice given to me by the dentist*’ 2) Perceived Manipulation: ‘*The advice given to me by the dentist is untrue or manipulated*’ and 3/4) Message Derogation: ‘*The advice given to me by the dentist is exaggerated*’ and ‘*I do not personally believe the advice given to me by the dentist*’ responses from *1*=*strongly disagree to 5*=*strongly agree*•Intention to change behaviour ‘*Before my next appointment I intend to*.[target behaviour]’ responses from *1* = *absolutely disagree to 5* = *absolutely agree*.

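### The mediation analysis names no baseline control on the path from EPPM variables to behaviour change, so that path is open to confounding by baseline behaviour

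*Protocol article*

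**What the plan says.** Section 2.13.2 (Analysis of behavioural outcomes) sets two pre-conditions for mediation, taken from a cited method. The first is that group is related to the EPPM mediators. The second is "that the mediator be linked to the criterion (behavioural change) controlling the predictor". Path analysis and a bootstrap test follow, and "All potential mediators will be assessed in the same analysis". There is an entry condition: "this analysis will be performed only where between group differences in behavioural change have been identified".

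The mediation sentence takes behavioural change as its criterion. For the group comparison, the same section speaks both of "predicting six and twelve-month follow-up scores from group membership" and of change: "Separate analyses will examine changes from baseline to 6 months and from baseline to 12 months".

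No baseline behaviour is named for the mediator-to-behaviour path. Section 2.13.3 (Analysis of clinical outcomes) does name the baseline value as a covariate for the three QLF variables. Table 1 shows that the baseline value exists: "Oral health behaviours: toothbrushing, diet, fluoride and smoking" is scheduled at Visit 1 and at every later time point.

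**The concern.** Randomisation protects the group-to-mediator path and the total effect of group on behaviour. It does not protect the mediator-to-behaviour path, because nobody is randomised to a level of self-efficacy or perceived threat.

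Baseline behaviour is an obvious candidate confounder. The self-efficacy item in section 2.9 reads "Please consider how confident you are that you can perform the behaviour properly, regularly and on a long-term basis". Answers to it will plausibly follow what the patient already does, and what the patient already does also predicts later behaviour and the room left for change. In the group comparison, leaving baseline out costs only precision. Here it can bias the estimate, and a bootstrap then puts an interval around a biased product.

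At stake is the third objective in section 2.3, which uses EPPM variables to predict behaviour change, and the stated aim in section 2.2 of understanding why a format works or fails.

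**Working it through.** **The plan's own figures.** The protocol gives none for mediation. Its sample size reproduces: 63 per arm for 0.5 SD, 145 per arm for 0.33 SD, and 106 analysable per arm with a 20% allowance gives 106/0.80 = 132.5, so 133.

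**Model.** G is group, Y0 baseline behaviour, M the mediator and Y1 follow-up behaviour. Y0, and M within group, have unit variance.

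- M = a·G + c·Y0 + u
- Y1 = rho·Y0 + b·M + d·G + e

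The documents give none of a, b, c, d or rho, so all are assumptions. Within group, Cov(M, Y0) = c. With only G controlled, the slope on M is therefore:

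- follow-up score: b + rho·c, a bias of rho·c
- change (Y1 − Y0): b + rho·c − c, a bias of (rho−1)·c

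With Y0 in the model, the slope is b for either outcome.

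**Size of the path bias and of false mediation.** Assumptions: b = 0, d = 0, rho = 0.5, a = 0.4 SD, two arms of 100. Mediation counts as found when both paths have p<0.05. The entry condition is not yet applied.

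| c | Bias, change | Bias, follow-up score | False mediation, group only | With baseline |
|---|---|---|---|---|
| 0.2 | −0.10 | +0.10 | about 23–25% | about 4% |
| 0.3 | −0.15 | +0.15 | about 45% | about 4% |
| 0.4 | −0.20 | +0.20 | about 62–65% | about 4% |

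**Applying the plan's entry condition.** The protocol does not define when a group difference counts as identified, so p<0.05 is assumed.

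- No group effect on behaviour (d = 0, b = 0): the condition is rarely met, and false mediation occurs in about 1–3% of all trials for c of 0.2 to 0.4.
- Direct effect d = 0.4 SD, b = 0, c = 0.3: the condition is usually met. False mediation occurs in about 36–38% of all trials, which is about 45% of those that pass, against about 4% with baseline adjustment.

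**Cancellation of a true effect.** With b = 0.20, c = 0.4 and rho = 0.5, the change-score slope is 0.20 + (0.5 − 1)·0.4 = 0.00. Before the entry condition, mediation is found in about 5% of trials, against about 71% with baseline adjustment. This compares the two models. It is not a rate per trial run: with no direct effect the total effect is only 0.4 × 0.20 = 0.08 SD, the entry condition is met in about 9–10% of trials, and even the adjusted model reports mediation in about 7% of all trials.

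**Sensitivity.**

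- Over c = 0.1 to 0.4 and rho = 0.3 to 0.7, the bias runs from −0.03 to −0.28 for change and from +0.03 to +0.28 for a follow-up score.
- At c = 0.1, false mediation before the entry condition is only about 9%.
- With 70 per arm (the 53% retention quoted in the Discussion, 0.53 × 133 = 70.5) and c = 0.3, it is 27–29%, against 4% when adjusted.
- In separate runs with a = 0.5 SD and c = 0 it is about 5%. With a = 0 it is at most about 3%.

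**The case against.** Four stronger readings are tempting, and the protocol does not support them.

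- **That the plan excludes baseline behaviour.** A reader might infer that group is the only permitted covariate. The text reports a pre-condition of a cited method in a condensed article, never says that group is the only control, and enters the other mediators in the same model. Section 2.13 also announces a detailed analysis plan. What stands is narrower: the protocol states one control for this path, and it is the wrong one to rely on. Joint entry of the mediators does not adjust for baseline behaviour.
- **That the path is confounded.** The documents do not quantify the relation between baseline behaviour and EPPM scores. If it is zero, there is no bias from this source. A false indirect effect also needs group to move the mediator, although section 2.2 expects just that.
- **That a quarter to two thirds of trials would falsely show mediation.** Those rates ignore the entry condition. When groups do not differ in behaviour, that condition removes nearly all of the problem. It does not help when a real direct effect opens the way.
- **That the mediation analysis itself uses two outcome forms with opposite biases.** The mediation sentence names only behavioural change. Follow-up scores appear in the paragraph on group effects, so the change-score bias is the one that applies directly.

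It is also fair that this analysis is secondary and explanatory.

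**Conclusion.** The concern holds in a limited form. The one control named for the mediator-to-behaviour path does not deal with baseline behaviour, and using change as the criterion shifts the bias to (rho−1)·c without removing it. In the setting where the analysis is most likely to be run, a direct group effect on behaviour, about 45% of the trials that reach the mediation step would falsely show mediation, against about 4% with adjustment. A true path can equally be cancelled. Both results rest on assumed slopes, a single-mediator model and p<0.05 as the entry condition. The simulated sizes show what is possible and do not predict this trial's result. The primary willingness-to-pay result and the randomised comparisons of behaviour are not affected.

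**What to change.** In section 2.13.2, state that the pre-information value of the same behaviour is a covariate in both the mediator equation and the behaviour equation, and that the bootstrap is applied to this adjusted indirect effect. Report the result as conditional on no remaining mediator-outcome confounding, since baseline adjustment cannot deal with unmeasured factors. Dental anxiety (MDAS) and other Visit 1 covariates are optional additions.

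No new data are needed, because Table 1 already schedules behaviour at baseline. The cost is a few extra model terms and a more cautious claim.
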